### Lexical/semantical analyses

The data obtained via 48 semi-directed interviews (the first two samples recruited in Strasbourg) will be analyzed using the software Iramuteq 0.7 (R interface for multidimensional analysis), which is designed to perform lexical/semantical analysis. First, we will extract the most listed characteristics, independently of grammatical form. Second, we will analyze specificities for each sub-group of patients. Third, to check if these specificities have a statistical meaning, we will extract relative occurrences (occurrences depending on the total number of words produced) for these characteristics and compare the number of relative occurrences for each type of subgroup, using the chi^2^ test.

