#### Objectives {7}

The primary objective of our study is to evaluate the efficacy of a 12-week CFT group in decreasing self-stigma associated with severe psychiatric disorders and ASD by comparing its immediate effects to the effects of the Ending Self-Stigma (ESS) psychoeducation program [29] and to TAU.

The secondary objectives of our study are as follows:1. To evaluate the maintenance of effects on self-stigma scores in the three groups of treatment (CFT, ESS, and TAU) at 6-month follow-up (V2)2. To assess the effects of treatment (CFT, ESS, and TAU) at baseline (V0), post-treatment (V1), and at 6 months follow-up (V2) on target psychological dimensions (shame, self-compassion, emotional regulation, automatic avoidance tendencies toward mental illness)3. To assess the effects of treatment (CFT, ESS, and TAU) at baseline (V0), post-treatment (V1), and at 6 months follow-up (V2), on social functioning and psychiatric measures (psychiatric symptoms, depression, anxiety and stress, social functioning, access to care, recovery, functional remission)4. To assess the psychological factors mediating (shame, self-compassion, and emotional dysregulation) the efficacy of CFT on the self-stigma measure (V1)5. To evaluate the acceptability of the active interventions (CFT and ESS): pretreatment (V0) via a treatment credibility measure, during treatment via attrition rate, session attendance and group cohesion, and post-treatment (V1) via patient satisfaction and treatment side effects In addition, in the coordinating center, qualitative interviews will assess the acceptability of the active interventions.

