### Recruitment {15}

A large network of professionals in institutions or in private practice (e.g., psychiatrists, psychologists) of the geographical area of all the participating centers of the study will be deployed to refer patients to the investigating teams. All the hospital centers are central coordinators of the care of patients with SMI and ASD in their respective areas; moreover, all of them propose care within a recovery model of psychiatric disorders. These factors guarantee that many patients with SMI and ASD can be recruited in these centers and that all centers will show high levels of implication in the recruitment and adherence to the psychotherapeutic models proposed.

Patients will be recruited into the psychiatric and mental health department of each center during a routine clinical consultation. The inclusion period is 48 months. This is a realistic duration given the significant number of patients to be enrolled. The study is scheduled to involve 7 French national centers, with 24 patients to be enrolled per center (one randomization blocks of 24 patients—3 groups of 8 patients in CFT, ESS, and TAU—in each center; the Strasbourg center will recruit 192 patients, i.e., 8 randomization blocks).

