
The mechanisms underlying the relationship between the intervention and the primary endpoint will be identified by carrying out an estimation of the causal mediation effect using the Baron and Kenny procedure though the quasi-Bayesian approximation. This allows for obtaining total, direct, indirect effects and the percentage of mediation. The potential mediators that will be tested include self-compassion, shame, and emotional dysregulation.

The statistical analyses will be run with the following software: R (with all the relevant packages), OpenBUGS, and JAGS, in their most up-to-date version at the time of analysis.

There is no significance level in Bayesian statistics. An effect will then be considered significant if its probability to exceed a prespecified threshold value, given the data, is strictly larger than 0.975 or strictly lower than 0.025. Credibility intervals will be provided at 95%.

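### The lexical analysis uses a chi-square test to confirm subgroup specificities on the same 48 interviews that produced them, with no stated safeguard against chance findings

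*Protocol article*

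**What the plan says.** The data set is described in the Protocol article, Lexical/semantical analyses: "The data obtained via 48 semi-directed interviews (the first two samples recruited in Strasbourg". Three steps are then run on it.

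- Step 1: "First, we will extract the most listed characteristics, independently of grammatical form". This selects on overall frequency; subgroup is not mentioned.
- Step 2: "Second, we will analyze specificities for each sub-group of patients". No cut-off, ranking or discard rule is given, and the subgroups are not defined here. Treatment arm is the natural meaning, because Outcomes {12} places the interviews in all three groups, but that is an inference.
- Step 3: "Third, to check if these specificities have a statistical meaning, we will extract relative occurrences", and then "for these characteristics and compare the number of relative occurrences for each type of subgroup, using the chi^2^ test".

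Objectives {7} gives the purpose of the interviews: "in the coordinating center, qualitative interviews will assess the acceptability of the active interventions". The section states no significance level for the chi-square test. The only decision rule in the statistical methods is the Bayesian one, introduced with "There is no significance level in Bayesian statistics".

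**The concern.** Step 3 is offered as a statistical check on what step 2 found, but it makes the same between-subgroup comparison in the same interviews. A word that stood out by chance in step 2 stands out again in step 3, because the counts are the same. The test therefore adds no independent evidence about a word that was noticed because it differed. Making the participant the unit of analysis would not cure this.

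At stake is what the report says about acceptability. Themes described as specific to CFT, ESS or TAU participants could be presented as statistically supported when they are chance contrasts.

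**Working it through.** **Inputs from the article.** Recruitment {15} describes a randomization block of 24 as "3 groups of 8 patients in CFT, ESS, and TAU". Two blocks give 2 × 24 = 48 interviews, which reproduces the stated number, and 2 × 8 = 16 per arm. The article gives no error rate for the lexical analysis, so there is no such figure to reproduce.

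**Assumed inputs.** A 5% level, the number of word forms, the number of words taken forward, and the interview length. None of these is in the article.

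**Reading A: only the specific-looking words are tested.** Two null simulations were run with 48 interviews, 16 per subgroup and no true difference.

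1. *Participant as the unit.* There were 100 or 300 word forms, the 5 most specific forms per arm were selected, and each was tested by Kruskal-Wallis at 5%, with 40 runs per setting.

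| Word use | 100 forms | 300 forms |
|---|---|---|
| Independent words | 26% | 49% |
| Varies between people | 19% | 31% |

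Unselected words were rejected 4 to 5% of the time. Each setting rests on at most 15 × 40 = 600 selected words. Treated as independent, these have a standard error of at most about √(0.49 × 0.51 / 600) = 0.02.

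2. *Chi-square on pooled word counts.* There were 50 or 100 frequent words with Zipf-type frequencies, 1000 words per interview (3000 in a check) and 400 replicates. A word was flagged if it was over- or under-represented in any subgroup at one-sided p < 0.05 (hypergeometric). With independent words:

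- all frequent words: 5.0 to 5.3% rejected;
- flagged words: 25 to 29% rejected;
- the 10 most contrasting words: 26% rejected (50 words) and 49 to 52% (100 words).

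The counts show the mechanism. With 50 words, an average of 9.8 are flagged and 25.9% of these are rejected: 9.8 × 0.259 = 2.5. Testing all 50 gives 50 × 0.051 = 2.6. With 100 words the figures are 18.4 × 0.288 = 5.3 and 100 × 0.053 = 5.3. So nearly all the false positives lie among the flagged words. Selection does not add any; it concentrates them in the words that are put forward.

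**Reading B: all the most-listed words are tested.** The per-word rate stays near 5% for independent words. The chance of at least one false positive among m independent tests is 1 − 0.95^m:

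| m | Chance of at least one |
|---|---|
| 10 | 0.40 |
| 20 | 0.64 |
| 50 | 0.92 |
| 100 | 0.99 |

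A flagged word has the same p-value whether or not the unflagged words are also tested. If the specific-looking words are the ones discussed, the 25 to 29% still applies to them under this reading.

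**A separate problem in the same test.** A chi-square on pooled occurrences treats words as independent although they cluster within 48 people. With assumed between-person variation (gamma variance 0.1 to 1.0), it rejected about 10 to 49% of frequent words under the null with no selection at all. This is a unit-of-analysis error and is not counted in the figures above.

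**The case against.** **Selection by contrast is not written down.** The only extraction rule is overall frequency in step 1, and the characteristics tested in step 3 are most literally those most-listed ones. This stands. A reader might infer that circularity is established, but the article never says that only specific-looking words are tested. Under the other reading the defect is uncontrolled multiplicity.

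**Testing fewer words cannot create extra false positives.** This also stands, as the counts show. In the participant-level simulation with independent words, 26% of 15 is about 4 and 49% of 15 is about 7, against 5 and 15 from testing all 100 or 300 forms at 5%. It does not rescue the step, because what is put forward as confirmed is a short list, and the error rate within that list is well above 5%.

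**The level and multiplicity rule may sit in an analysis plan that is not shown.** Their absence alone would not be a finding. The stated sequence is: a test described as checking specificities, run on the data that suggested them.

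**The sizes rest on assumptions.** They do, and selecting the most contrasting words is itself one of them. A reader might also quote rejection rates near 100% for selected words under the pooled chi-square. Those appear only when word use varies between people, so they mix selection with clustering and do not measure circularity.

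**The consequence is small.** Acceptability is also assessed by credibility, group cohesion, satisfaction, attendance and drop-out. A reader might infer that the efficacy or mediation results are compromised. They do not use these data.

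**Conclusion.** The concern holds in a limited form. As written, step 3 can present chance differences between subgroups as statistically confirmed, under either reading of which words are tested.

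- If only specific-looking words are tested, about 20 to 50% of the selected words are significant under the null with the participant as the unit, against about 5% of unselected words.
- If all most-listed words are tested, the per-word rate is near 5% for independent words, but at least one false positive has probability about 0.40 for 10 words and 0.92 for 50.

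The direction does not depend on the assumed vocabulary size, number of words selected or 5% level; the percentages do. The effect is confined to the single-center qualitative acceptability analysis. It does not follow that false themes will be reported, only that the test would not prevent it.

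**What to change.** Choose one of two changes to the Lexical/semantical analyses section.

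1. Report the subgroup specificities as descriptive and exploratory, without significance tests. This needs only a change of wording.
2. Keep a test, but define the subgroups, state which words are tested, and make the participant the unit. Obtain p-values by permuting participants' group labels within each of the two Strasbourg samples and rerunning the whole selection-and-test sequence for every permutation. This needs a short script and no further interviews.

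The cost of the second option is that fewer words will be called significant. Selecting words on one Strasbourg sample and testing them on the other is not recommended: it leaves 24 interviews for the test, about 24 / 3 = 8 per arm.

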To evaluate the *acceptability* of the active interventions (CFT and ESS):• The Credibility and Expectations Questionnaire [68, 69] will be applied to assess self-reported treatment credibility at V0. This questionnaire contains 6 items rated either from 1 to 9 or from 0 to 100% and evaluates whether the participants “think” or “feel” that their treatment will be efficient.• The Group Questionnaire [70] will be used to measure group cohesion 3 times during the intervention (sessions 1, 6, and 12). It consists of 30 items addressing the group leaders, the other group members, and the group in general. Each item is scored using a scale ranging from 1 (not true at all) to 7 (very true).• The Consumer Satisfaction Questionnaire for Psychotherapeutic Services (CSQ-8) [71] will be applied as a self-report measure assessing participants’ satisfaction at the end of the 12-week program. The 8 items are scored on a scale ranging from 1 to 4. Higher scores are indicative of elevated satisfaction.• The attendance rate will be determined by the number of group sessions attended by the patient, and the drop-out rate will be determined by the number of patients lost to follow-up in each arm. In addition to the Consumer Satisfaction Questionnaire for Psychotherapeutic Services questionnaire (CSQ 8) [71], the avoidance of participants (due to self-stigma) in several social situations during the last 6 months, and the satisfaction with the interventions will be assessed via semi-structured interviews conducted at V2 by clinician-researchers blind to the status of patients (in the Strasbourg center only, for the 3 groups—CFT, ESS, and TAU).

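### The chi-square test on word occurrences in the interview analysis ignores that words are clustered within participants, so it is not valid however the counts are formed

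*Protocol article*

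**What the plan says.** Under Lexical/semantical analyses the data source is given as "The data obtained via 48 semi-directed interviews (the first two samples recruited in Strasbourg". The most frequent terms are extracted first. Then comes a step worded as "Second, we will analyze specificities for each sub-group of patients". Last, to decide whether those specificities are statistically meaningful, the plan takes "relative occurrences (occurrences depending on the total number of words produced) for these characteristics" and will "compare the number of relative occurrences for each type of subgroup" by means of a chi-square test.

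Two other sections supply context. Recruitment {15} describes a randomization block of 24 as "3 groups of 8 patients in CFT, ESS, and TAU". Secondary outcomes states that the interviews are held "in the Strasbourg center only, for the 3 groups". The lexical section does not define the subgroups, name a significance level, give the number of terms or the words per interview, or mention a participant-level unit or a correction for clustering. By contrast, the primary model under Statistical methods {20a} carries a random effect for the subject.

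**The concern.** A chi-square test of term occurrences against total words treats each word as an independent observation. It is not one: a participant produces hundreds or thousands of words, and someone who favours a term repeats it. The effective sample size is set mainly by the number of people, not the number of words. One or two participants can drive a cell.

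The wording adds a second problem. A relative occurrence is a rate, not a count. A chi-square statistic computed on rates changes with the unit in which the rate is expressed, so its p-value has no fixed meaning.

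At stake are the vocabulary specificities that would be reported for subgroups of the single-center interviews. This is the only test specified for those interview data, which cover avoidance and satisfaction.

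**Working it through.** **Sample.** Two blocks × 3 arms × 8 participants = 48, which matches the stated number of interviews. If the subgroups are the arms, each has 2 × 8 = 16 participants. The protocol states no error rate or power for this test, so there is no such figure to reproduce.

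**Assumed inputs** (none is in the protocol): two-sided alpha 0.05; m = 1,500 words per interview, varied from 500 to 3,000; term share p = 0.005 (5 uses per 1,000 words); between-person coefficient of variation (CV) of term use from 0 to 1.0; no true difference between three subgroups of 16.

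**Reading 1: occurrences summed by subgroup.** The within-person correlation is rho = CV² × p/(1 − p). The variance is inflated by DEFF = 1 + (m − 1) × rho. The 5% critical value on 2 degrees of freedom is 5.991, so the actual rejection rate is approximately exp(−2.996/DEFF).

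For CV 0.5 and m = 1,500: rho = 0.25 × 0.005/0.995 = 0.001256; DEFF = 1 + 1,499 × 0.001256 = 2.88; exp(−2.996/2.88) = 35%.

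| CV | rho | DEFF (m = 1,500) | Rejection under the null |
|---|---|---|---|
| 0 | 0 | 1.00 | 5% |
| 0.3 | 0.000452 | 1.68 | 17% |
| 0.5 | 0.001256 | 2.88 | 35% |
| 0.7 | 0.002462 | 4.69 | 53% |
| 1.0 | 0.005025 | 8.53 | 70% |

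Simulation with gamma-distributed participant rates and Poisson counts agrees with the closed form to within about one percentage point.

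Over interview lengths of 500 to 3,000 words with CV 0.3 to 1.0, the ends of the range are:
- m = 500, CV 0.3: DEFF = 1 + 499 × 0.000452 = 1.23, giving 9%.
- m = 3,000, CV 1.0: DEFF = 1 + 2,999 × 0.005025 = 16.07, giving 83%.

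The level is held only at CV = 0, when every participant uses the term at the same underlying rate.

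**Reading 2: normalised rates entered as counts.** With the same simulated data and CV 0.3 to 1.0, rejection under the null is 0% for rates per 100 words and at most about 0.1% per 1,000 words. Per 10,000 words it runs from 0.3% (m = 3,000, CV 0.3) to 50% (m = 500, CV 1.0). The data are identical; only the unit differs.

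**Participant as the unit.** A Kruskal-Wallis test on each participant's relative frequency, 16 per subgroup, rejects in 4% to 6% of null runs across these settings.

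**The case against.** A reader might infer that differences between trial arms will be declared far too often. The protocol does not support that stronger statement, for three reasons.
- The subgroups are never said to be the arms. Arm is the natural reading, since all three are interviewed, but the diagnostic groups listed under Sequence generation {16a} are another possibility.
- Summing counts by subgroup is not stated. If rates per 100 or per 1,000 words are used instead, the test would hardly ever reject.
- The size of any inflation depends on word counts, term frequency, between-person variation and alpha, none of which is given.

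It can also be said that the interviews are an add-on in one of seven centers, covering 48 of 336 participants. Objectives {7} introduces them as an addition, and acceptability is also measured by questionnaires, attendance and drop-out. That is correct and limits the consequence.

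A further defence is that a condensed article leaves such detail to the full protocol or analysis plan. This holds for the number of terms and the construction of tables. It does not hold for the test itself, which the article names together with its purpose. Nor does a participant-level rank test bring frequentist inference into an otherwise Bayesian plan, because the chi-square test has already done so.

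**Conclusion.** The point stands in a limited form. The named test does not respect the independent unit, and neither way of forming its input rescues it. With summed occurrences the error rate exceeds the nominal level as soon as participants differ in term use: about 17% to 70% for CV 0.3 to 1.0 at 1,500 words, and about 9% to 83% over 500 to 3,000 words. With rates treated as counts, the result is an artefact of scale, from about 0% to about 50%. The direction of error is therefore certain only on the first reading, and every magnitude rests on assumed inputs.

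The primary and main secondary conclusions are untouched. What cannot be relied on is a statement that a subgroup's vocabulary is statistically specific.

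**What to change.** Rewrite the final step of Lexical/semantical analyses to do the following:
- State which subgroups are compared, for example the three arms.
- Compute each participant's relative frequency of a term and compare subgroups with a Kruskal-Wallis or permutation test. Alternatively, model the participant's count with a negative-binomial regression and log(total words) as offset.
- Label the results exploratory, because the terms are chosen from the same interviews in which they are then tested.

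The participant is the minimum unit: if arms are compared, the 16 interviewees in each active arm come from only two therapy groups of 8, which the text should acknowledge.

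If no test is wanted, remove the chi-square test and report the lexical findings as descriptive only.

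The cost is a few lines of analysis text and code, with no change to data collection. The downside is that fewer terms can be expected to reach significance than with summed counts.

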### Interim analyses {21b}

Stopping of the trial could also be based on interim data analysis if clearly one treatment is better than the other, but no interim analysis is planned.

### Methods for additional analyses (e.g., subgroup analyses) {20b}

No additional analyses are planned.

### Methods in analysis to handle protocol non-adherence and any statistical methods to handle missing data {20c}

Subjects with at least one non-missing data, for a given analysis, will be included in the analysis.

In order to minimize attrition bias, an intention-to-treat analysis and specific techniques for handling missing data will be performed.

Missing data frequency will be listed for every variable. A univariate and bivariate (i.e., for each relevant group) description will be provided. Monotone patterns will be looked for and a probable missing data mechanism (completely at random, at random, or not at random) will be identified.

Missing data will be treated according to their frequency in a given analysis. Simple deletion will be considered if the proportion of missing data is smaller than 3%. For a missing data proportion between 3 and 20%, multiple imputations will be used. For larger proportions of missing data, the relevance of each analysis will be discussed and, if required, specific models will be used.

Multiple imputations will be implemented and run directly within the Bayesian model scripts.

### Plans to give access to the full protocol, participant-level data, and statistical code {31c}

The consent form, information material, and database are available from the corresponding author on request.

### Oversight and monitoring

#### Composition of the coordinating center and trial steering committee {5d}

The coordinating center in Strasbourg will be led by MR, SW, and LW and include 2 additional psychologists. Their role is to supervise the inclusion process (communication, information of potential recruits, consent) and to explain and guide the other centers in their own inclusion and assessment process, providing standardized documents for the inclusion call, communication means, and data storage. The psychotherapy coordinating team (LW, MR) will also hold monthly supervision sessions to increase adherence to the psychotherapy models. This coordinating group will meet weekly. A scientific committee, composed of the main investigator (LW), associated scientific member and investigator (MR), the methodologist (LF), and a promoter representative, wrote the protocol, selected the investigators, and will decide whether to modify, continue, or stop the project.

